### CONSORT Diagram

The CONSORT Diagram, which will be used to illustrate recruitment and loss during the study, can be found in Fig. 1. For a further detailed breakdown of the patient involvement in the study, Fig. 2 shows the SPIRIT flowchart of the trial.

**Fig. 1 Fig1:**
[figure not shown]
CONSORT Diagram for TOPCAT-G feasibility study

**Fig. 2 Fig2:**
[figure not shown]
CONSORT Diagram for TOPCAT-G feasibility study

### Measures

#### Primary outcome measures

The primary outcome measures of the feasibility trial will be:Patient recruitment rateThis will be calculated from the total number of eligible patients invited to take part in the study and the number of patients giving written consent to participate in the study.Patient attrition rateThis will be calculated from the number of patients who gave written consent and the number of patients who have completed any measures, regardless of their completion rate.

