### Participants

#### Inclusion criteria

We propose to recruit a cohort of female patients who have completed treatment for cervical, endometrial, epithelial ovarian, or vulval cancer within the last 3 months in BCUHB in North Wales. Patients who have completed treatment for fallopian tube and primary peritoneal carcinoma will also be included. The cohort will be identified through the regional gynaecological cancer multidisciplinary team meeting (MDT) records and will consist of patients who are considered fit for taking part in the trial and able to give informed consent, as assessed by the MDT. Patients may have received surgery, chemotherapy, radiotherapy or a combination of these. At the time of entry, patients in the view of their treating consultant will not have a definite need for continued hospital-based care.

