### Sample size

We estimate 30% will not fit the inclusion criteria whilst an unknown proportion of the remainder will not enter the study, either through not wishing to consent or for other reasons. The extent of patient acceptability is unknown but for planning purposes, we will assume 50% acceptance. Assuming a throughput of approximately 150 newly diagnosed cases, we hope to randomise 50 participants from the recruiting centres into the study during a period of 6 months. It is thought this would be sufficient to inform a sample size of a future full trial [35] and enable a reasonably diverse group to fully assess the acceptability of the trial.

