#### Secondary outcome measures

A single booklet of outcome questionnaires will be provided to all trial participants at baseline and 6 and 9 months post-treatment. These are as follows:EORTC QLQ-C30This is a validated measure to assess the quality of life of cancer patients [41]. It comprises a 30-item questionnaire incorporating five functional scales (physical, role, cognitive, emotional and social), three symptom scales (fatigue, pain and nausea and vomiting), a global health status/quality of life scale and a number of single items assessing additional symptoms commonly reported by cancer patients and perceived financial impact of the disease.EQ-5D-3LThis is a validated generic, health-related, preference-based measure comprising five domains: mobility, self-care, usual activities, pain and discomfort and anxiety and depression. Each domain has three levels (no problems, some problems and a lot of problems). The EQ-5D-3L scoring system defines 243 possible health states. The questions are complemented by a visual analogue scale (VAS), on which respondents are asked to indicate their current health [42].ICECAP-A (ICEpop CAPability measure for Adults)This is a measure of capability for the general adult population [43]. The ICECAP-A covers five attributes of wellbeing: attachment, stability, achievement, enjoyment and autonomy.Client Service Receipt Inventory (CSRI)This is an adapted version of a standardised measure using self-report service user data to evaluate and cost service use, including all GP visits and unscheduled secondary care in both arms of the study [44, 45].

Additional data to be captured will include the following:e)Patient demographics, cancer type and stage, type of treatment received and co-morbidity at baseline (from medical records and patient confirmation).f)Data on the pattern, timing and method of detection of relapse and on survival (recorded using a Serious Adverse Events form).

We anticipate that on average patients would complete all questionnaires in about 20 min on each occasion.

The number of patients offered the study will be logged to identify the proportion of patients that decline to take part. Patients who decline to consent will be asked if they would be willing to provide any reason(s) why they preferred not to take part.

Data will aim to be collected from all willing participants, even in the case of a withdrawal or non-compliance with the intervention.

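### The feasibility rule tests consent among invited women and has no accrual criterion, so it can pass while the trial misses its own target of 50 in 6 months

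*Protocol article*

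**What the plan says.** Four parts of the protocol article bear on this.

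- **Sample size.** The planning starts from a case flow: "Assuming a throughput of approximately 150 newly diagnosed cases". It removes the ineligible ("We estimate 30% will not fit the inclusion criteria") and then says that "an unknown proportion of the remainder will not enter the study, either through not wishing to consent or for other reasons". For that loss, "for planning purposes, we will assume 50% acceptance". The result is the target: "we hope to randomise 50 participants from the recruiting centres into the study during a period of 6 months".
- **Primary outcome measures.** The recruitment rate is "calculated from the total number of eligible patients invited to take part in the study" (denominator) and the number who give written consent (numerator).
- **Statistical methods.** A full RCT counts as feasible if the recruitment rate and the retention rate are each at least 50%. Eligibility and questionnaire completion rates are also calculated, as supporting evidence outside the rule. The rule contains no number recruited, no accrual per month and no share of eligible women invited.
- **Recruitment and Secondary outcome measures.** Staff identify women from hospital databases against the criteria, and eligible women are to be approached and invited. In addition, "The number of patients offered the study will be logged to identify the proportion of patients that decline to take part".

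**The concern.** The same 50% is used on two bases. In the sample size it is a share of all women who meet the criteria. In the primary outcome it is a share of those who were also invited. The two agree only if every eligible woman is invited. An eligible woman who is never approached counts as a loss in the planning but disappears from the primary outcome.

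A proportion also says nothing about volume. Even if everyone eligible is invited, half of a smaller pool still meets 50%.

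The rule decides whether a full trial is called feasible, and the protocol's aim ties feasibility to the ability to recruit and retain. A pass that coexists with a missed recruitment target would carry an optimistic accrual assumption into the number of centres and the duration of the full trial.

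**Working it through.** **Inputs.** From Sample size: about 150 cases, 30% ineligible, 50% acceptance, target 50 in 6 months. From Primary outcome measures: consents over eligible women invited. From Statistical methods: threshold 50%. From Background: 92 ovarian, 107 endometrial and 35 cervical cases in the health board in 2014. Consents are treated below as equal to randomisations.

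**1. The plan's own figure.** Eligible: 150 x (1 - 0.30) = 105. Recruited: 105 x 0.50 = 52.5, close to the stated 50. The figure is reached only if the 50% applies to all 105.

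**2. First route: incomplete invitation.** If a share *s* of the 105 is invited and exactly 50% of them consent, the rule is met with 105 x *s* x 0.50 consents. The protocol gives no value for *s*, so the range is assumed.

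| Share invited (assumed) | Invited | Consents at 50% | Share of all eligible |
|---|---|---|---|
| 100% | 105 | 52.5 | 50% |
| 90% | 94.5 | 47.3 | 45% |
| 80% | 84 | 42 | 40% |
| 70% | 73.5 | 36.8 | 35% |
| 60% | 63 | 31.5 | 30% |

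The break-even share is 50 / 52.5 = 95%. Below it, a rate of 50% passes and the target is missed. For example, 32 consents from 63 invited is 50.8%, a pass, but 32 / 105 = 30.5% of eligible women.

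A higher consent rate narrows the gap but need not close it. With a true consent probability of 0.6 (assumed), the exact binomial probability of passing with fewer than 50 consents is 0.39 for 84 invited, 0.86 for 74 and 0.945 for 63. With all 105 invited it is 0, because a pass then needs at least 53 consents.

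**3. Second route: lower throughput with full invitation.** The listed cases sum to 92 + 107 + 35 = 234 a year, or 117 per 6 months. Then 117 x 0.70 = 81.9 eligible, and 81.9 x 0.50 = 41 recruits. The rate is 50% and the rule passes, 9 short of target. Reaching 50 from this pool would need 50 / 81.9 = 61% consent.

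Vulval cases are not in the 234. As a rough allowance, the Background's UK figures give 1200 / (8500 + 7000 + 3000) = 6.5%. If that ratio held locally (assumption), it would add 234 x 0.065 = 15 a year, or about 7.6 per 6 months. Then (117 + 7.6) x 0.70 x 0.50 = 43.6, still below 50.

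**4. What each change would repair.** With 105 eligible and all of them in the denominator, the threshold needs 53 consents, so a pass secures the target; this closes the first route. It does not close the second: with about 82 eligible the threshold needs only 41. That route needs a criterion on the number randomised.

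**The case against.** The strongest reply is that, as planned, the two denominators are the same group. The Recruitment section says that eligible women will be approached and invited, and Sample size calls its 50% acceptance, which reads naturally as a rate among those asked. Consent among the invited is also a legitimate and common feasibility measure. All of this stands. It means that the first route opens only if invitation falls short, and that the table shows a range, not a forecast. It leaves the second route untouched, because there every eligible woman is invited.

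A further reply is that the eligibility rate, the log of offers and the CONSORT diagram (figure not shown) already cover the matter. They may well make consented/eligible derivable. None of them enters the decision rule.

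Two stronger readings are tempting and are not supported:

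- A reader might infer that the invited denominator hides consultants holding patients back. Inclusion criteria makes the consultant's judgement part of eligibility: "patients in the view of their treating consultant will not have a definite need for continued hospital-based care". A woman held back on that ground is ineligible, so she is outside either denominator. The eligibility rate is where she would show.
- A reader might infer that the other reasons for not entering, mentioned in Sample size, mean never being approached. The text does not say so. An invited woman who does not consent for some other reason stays in the stated denominator.

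**Conclusion.** The point holds in a limited form. The article itself fixes the recruitment definition and the decision rule, and together they allow a full trial to be called feasible while this trial misses its target of 50 in 6 months.

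The absence of an accrual criterion is the more robust part. It needs no assumption about invitation, only a throughput below 150. The protocol's own case counts point that way: about 41 recruits per 6 months at 50%, or about 44 with a rough allowance for vulval cancer. Both figures rest on 2014 counts, an even flow over the year and the planning rates of 30% and 50%.

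The denominator is the conditional part. It matters at 50% consent only if fewer than about 95% of eligible women are invited, and the documents give no reason to expect any particular share. They do not show that the recruitment rate will be overstated, only that the rule could not detect it.

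**What to change.** 1. Define the recruitment rate used in the rule as consented over all eligible women identified from MDT records and hospital databases in the recruitment window, and apply the 50% threshold to it.
2. Report invited/eligible and consented/invited beside it. The second keeps the acceptance rate that the protocol now defines.
3. Add the number randomised in 6 months, against the target of 50, to the feasibility rule.
4. State in advance how the two criteria combine. They can disagree in both directions: 50 of 105 meets the target but is 47.6%, while 41 of 82 is 50% but misses the target.

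The cost is small. Women are already identified from these sources, so the addition is a screening-log count of eligible women not invited. The downside is a recruitment figure that may look less favourable. If every eligible woman is invited, item 1 leaves the rate unchanged.

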### Recruitment

All patients will be recruited from three hospitals in the North Wales Cancer Network: Ysbyty Gwynedd, Ysbyty Glan Clwyd, and Ysbyty Maelor. The research nurse and three clinical nurse specialists (CNSs) will identify women from the hospital databases, in line with the inclusion and exclusion criteria above. Eligible patients will be approached by the clinic medical team and/or by the research nurse/CNS and will be invited to take part in the study. Patients will be given a participant information sheet at their end-of-treatment visit and will have until their follow-up appointment to consider the study (usually around 6 weeks), and those who would like to participate will have the opportunity to contact the research nurse by phone or email for more information before their follow-up appointment. Patients will be informed that if they agree to participate, they will be randomly assigned to one of the two treatment groups, both receiving slightly different modes of follow-up support. After agreeing to take part in the study, patients will give written consent at their 3-month routine follow-up appointment.

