### Randomisation

Following their 3-month appointment, consenting patients will complete the baseline measures (see below) then be randomised at the end of the 3-month review appointment. Patients will be randomised on a 1:1 ratio by the North Wales Organisation for Randomised Trials in Health (NWORTH) using a dynamic, independent, secure, web-based, randomisation procedure that can be accessed 24 h a day [36]. Patients will be randomised to one of the two arms of the study: standard care or nurse-led intervention. Site and disease type will be included as stratification variables. The participants, research nurse, CNSs and trial management will be unblinded during this trial. All other members of the team, especially the trial statistician, will remain blinded.

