### Standard care

After patients have been allocated to the standard care arm of the study, they will be informed about the next part of the study and their 6- and 9-month appointments scheduled. Patients randomised to standard care will continue to have their usual hospital-based doctor-led medical reviews (at 6 and 9 months post-treatment conclusion) and will be followed up according to an agreed protocol with the regional gynaecological cancer MDT and representing current practice. This will include an agreed protocol on further blood tests and scans if considered appropriate to routine follow-up.

In addition to their usual follow-up appointments, patients will be asked to complete a set of outcome questionnaires at baseline (following consent, but prior to randomisation), with assistance from the research nurse or CNS at the 3-month follow-up appointment. Patients will then be asked to complete the same set of outcome measures at the end of each of their follow-up appointments. If this is not possible, then the research nurse will send the questionnaires by post for completion and return in a self-addressed, pre-stamped envelope.

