In addition to the nurse-led intervention, patients will be asked to complete the same set of outcome questionnaires as patients in the standard care arm. The outcome questionnaires will be completed at baseline (prior to randomisation) with assistance from the research nurse or CNS at the 3-month follow-up appointment. Patients will receive the same set of outcome questionnaires by post at 6 months post-treatment and within a week of their 9-month telephone follow-up and will be asked to return them in a self-addressed, pre-stamped envelope.

For this study, we will consider the study endpoint to be the 9 months post-treatment data collection. After the 9-month data collection point, the intervention and control arm patients will continue with follow-up care as the clinician advises and is available to the local service.

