### Statistical methods

Descriptive statistics will be reported, including clinical and demographic characteristics of those recruited. To assess the feasibility of a full RCT, the recruitment and retention rates will be calculated. A future full RCT will be considered feasible if the recruitment rate is at least 50% and retention rate is no less than 50%. Additionally, the patient eligibility rate and questionnaire completion rates will be calculated to provide further evidence for the appropriateness of a full trial and associated measures.

Exploratory analysis will also be conducted around the assessments of QoL with the purpose of estimating key parameters for powering the main RCT but not to provide definitive results for the study. Effect sizes of the differences in final scores calculated from the EORTC QLQ-C30 will be calculated between the groups as randomised for the study endpoint. The effect size will be used to inform future sample size calculations for a larger, multi-centre RCT.

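### As worded, the primary attrition rate can be satisfied by the baseline booklet alone, so the 50% retention criterion would in practice be met whatever is returned at 6 or 9 months

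*Protocol article*

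**What the plan says.** All places are in the protocol article.

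- **Primary outcome measures** gives the only definition of attrition. The rate is calculated from "the number of patients who gave written consent and the number of patients who have completed any measures, regardless of their completion rate". No time point is attached.
- **Recruitment** fixes when consent is given: "patients will give written consent at their 3-month routine follow-up appointment".
- **Randomisation** fixes the order at that visit: "consenting patients will complete the baseline measures (see below) then be randomised at the end of the 3-month review appointment".
- **Standard care** places the first questionnaires "at baseline (following consent, but prior to randomisation), with assistance from the research nurse or CNS at the 3-month follow-up appointment". **Nurse-led intervention** says the same for the other arm: "The outcome questionnaires will be completed at baseline (prior to randomisation) with assistance from the research nurse or CNS".
- **Secondary outcome measures** counts baseline among the booklet's time points: "A single booklet of outcome questionnaires will be provided to all trial participants at baseline and 6 and 9 months post-treatment".
- **Nurse-led intervention** sets the endpoint: "we will consider the study endpoint to be the 9 months post-treatment data collection".
- **Statistical methods** sets the decision rule: "A future full RCT will be considered feasible if the recruitment rate is at least 50% and retention rate is no less than 50" per cent. Retention is not defined there. Questionnaire completion rates are to be calculated as additional evidence, with no threshold.
- **Discussion** says that feasibility will be judged on recruitment and attrition.

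**The concern.** A retention rate should show how many women are still providing data when the trial needs them, which here is 9 months. The stated rate counts a woman as retained once she has completed any measure, and the first measure comes before randomisation, with a nurse present. A woman who consents, completes baseline, is randomised and is never heard from again is therefore not counted as lost.

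This matters because the rate is both a primary outcome and one of the two tests for going on to a full RCT. The Aim section ties feasibility to retaining patients and to collecting data regularly, and the planned QLQ-C30 effect size is taken at the study endpoint. Followed as written, the retention test could be reported as passed without saying anything about loss to that endpoint.

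**Working it through.** **Inputs from the protocol article.** Throughput about 150, 30% not meeting the inclusion criteria, 50% acceptance, target 50 randomised (Sample size). Attrition definition (Primary outcome measures). Threshold of 50% for retention (Statistical methods). Visit order: consent, baseline, randomisation (Recruitment, Randomisation).

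**Step 1: the planned number.** 150 × (1 − 0.30) × 0.50 = 52.5, against a stated target of 50. Since the throughput is given as approximate, the two agree well enough, and 50 is used below.

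**Step 2: the rate as worded.** The document gives no other definition, so take

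retention = 1 − attrition = (consenters with at least one completed measure) / (all consenters).

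If the visit order is followed, all 50 randomised women have a baseline measure. If nobody else consented, retention = 50/50 = 100% and attrition = 0%. Returns at 6 and 9 months do not enter the formula. For illustration, suppose that 15 of 50 return a 9-month booklet. The rate as worded is still 100%, while retention at 9 months is 15/50 = 30%. If none return it, the two figures are 100% and 0%.

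**Step 3: what would make the criterion fail.** Only women who consent but complete no measure can lower the rate. With 50 randomised and x such women, retention = 50/(50 + x):

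| x | Retention as worded |
|---|---|
| 1 | 98.0% |
| 5 | 90.9% |
| 10 | 83.3% |
| 50 | 50.0% (still passes) |
| 51 | 49.5% (fails) |

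Put as a probability, take 50 consenters and assume that 2%, 5% or 10% complete no baseline and nothing later. Expected retention is 98%, 95% or 90%. The binomial probability of at least 25 of 50 is about 100% in each case.

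**Step 4: the same threshold applied at 9 months.** Let X be the number of 50 women who return a 9-month questionnaire, X ~ Binomial(50, p). The criterion is met if X ≥ 25. The documents give no expected retention, so p is assumed over a range:

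| Assumed 9-month retention p | P(X ≥ 25) |
|---|---|
| 30% | 0.2% |
| 40% | 9.8% |
| 50% | 55.6% |
| 60% | 94.3% |
| 80% | about 100% |

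Counted at 9 months, the rule separates poor from adequate retention. Counted as worded, it passes with near certainty in every row.

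**The case against.** The strongest reply is that the authors meant follow-up measures. Attrition ordinarily means loss over follow-up, the endpoint is set at 9 months, and the closing phrase of the definition seems aimed at partly completed booklets rather than at baseline. That may well be the intention. But no sentence ties attrition or retention to 6 or 9 months, and the phrase about completion supplies no time point. On the kinder reading, the wording still has to change.

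A second reply is that losses will show elsewhere: the CONSORT diagram is to illustrate loss during the study, and completion rates will be reported. An almost empty 9-month dataset would indeed be visible. Neither item carries a threshold, however, and neither alters the feasibility rule. Nor is this a detail left to the SAP, because the protocol states the definition itself and an SAP that followed it would inherit the problem.

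Some stronger readings are tempting but not supported:

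- **The test cannot fail.** True in practice, not strictly, as Step 3 shows. It also depends on reading retention as 1 minus attrition. That is an inference, though the only one the text offers.
- **The rate cannot be split by arm because its denominator is women who consented.** Every randomised woman has an arm, and nothing prevents a split. Consent and randomisation fall at the same appointment, so the two denominators should nearly coincide.
- **The full trial's dropout allowance will be wrong.** The document does not say that this rate will set such an allowance. The sample-size inputs it names are standard deviations and effect sizes.
- **A return should count only if the QLQ-C30 can be scored.** The authors explicitly chose to count returns however complete they are. That choice can stand.

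**Conclusion.** The point holds for the definition as worded. A baseline booklet alone makes a woman retained, so with the visit order followed the rate would be near 100% regardless of later returns. The 50% criterion would in practice be met automatically, failing only if more than half of consenters completed no baseline measure. This is a stated rule for a primary outcome that gives an uninformative feasibility result if followed, and it should be corrected before the criterion is applied.

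The conclusion rests on two assumptions: that retention is the complement of the stated attrition rate, and that baseline is completed at the consent visit as described. The 9-month retention values and the shares of consenters without a baseline used above are illustrative, not taken from the document.

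**What to change.** In Primary outcome measures, define retention as the number of randomised women who return any outcome questionnaire at the 9-month study endpoint, complete or partial, divided by all women randomised, with attrition as its complement. In Statistical methods, state that the 50% criterion applies to that rate.

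Report 6-month retention and the split by arm as supporting data, and show any loss between consent and randomisation separately.

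The cost is wording only, since the booklet is already scheduled at baseline, 6 and 9 months. The one downside is that the reported retention figure will be less favourable than under the present definition.
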